### 2.2. Secondary objectives

1. Evaluate the effect of the different components of the intervention, alone or combined, on (i) the vaccination intention of adolescents, parents and GPs, and (ii) knowledge, attitudes, beliefs and practices on infection and HPV vaccination of adolescents, parents, and GPs (including history of vaccine hesitancy), using the KABP-6C questionnaire.
2. Evaluate the impact of the socio-economic level of parents on the effectiveness of the different components of the intervention, alone or combined, on VC in adolescents aged 11-14 years.
3. Evaluate the efficiency (cost-effectiveness) of the different components of the intervention, alone or combined, among adolescents aged 11-14 years.
4. Evaluate the budgetary impact of the different components of the intervention, alone or combined. Note that this objective will only be carried out if the intervention under evaluation is cost-effective (secondary objective 3).
5. Evaluate the implementation of the different components of the intervention, and identify the levers and barriers to implementation at the individual and collective level to assess the transferability of the intervention to other contexts.

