A KABP-6C survey, at the individual level, repeated cross-sectionally (pre and post interventions) will make it possible to answer secondary objective 1 of the PrevHPV trial and thus to assess knowledge, attitudes, beliefs and practices. The KABP-6C questionnaire will be administered to volunteers in the following populations:

- Students, girls and boys, enrolled in Grades Eight and Nine in one of the public or private middle schools in the 90 municipalities of groups 1 to 6 before the implementation of the components in middle schools (December 2020) and after (May 2021).
- Parents, fathers and mothers of girls and/or boys enrolled in Grades Six through Nine in one of the public or private middle schools in the 90 municipalities of groups 1 to 6 before the implementation of the middle school components (December 2020) and after (May 2021).
- GPs practicing regular consultations with adolescents in the 60 municipalities of groups 1, 2, 5 and 6 before the implementation of the component (December 2020) and after (April 2021).

Costs and implementation indicators are collected prospectively by the referent of each middle school with the help of the PrevHPV project manager of the geographical sector concerned, as the different components of the intervention are implemented.

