## 5. SELECTION OF THE POPULATION

### 5.1. Populations under study

- **The target populations of the intervention are:**

- (i) GPs practicing in the municipalities randomized to groups 1, 2, 5,
- (ii) Middle school students enrolled in middle schools located in municipalities randomized to groups 1, 2, 3 and 4,
- (iii) Parents of middle school students attending middle schools located in municipalities randomized groups 1, 2, 3 and 4.

| Groups                                                   | Target populations | Middle school students | Parents of middle school students | GPs |
|----------------------------------------------------------|--------------------|------------------------|-----------------------------------|-----|
| Group 1 - EMM + Facilitation of access + Training of GPs |                    | X                      | X                                 | X   |
| Group 2 - EMM + Training of GPs                          |                    | X                      | X                                 | X   |
| Group 3 - EMM + Facilitation of access                   |                    | X                      | X                                 | /   |
| Group 4 – EMM                                            |                    | X                      | X                                 | /   |
| Group 5 - Training of GPs                                |                    | /                      | /                                 | X   |
| Group 6 - No intervention                                |                    | /                      | /                                 | /   |

*Populations targeted by the PrevHPV trial*

The effect of the intervention will be evaluated on:

- (i) Adolescents (girls and boys) aged 11 to 14 residing in the 90 municipalities participating in PrevHPV research (primary and secondary objectives),
- (ii) Parents of middle school students attending a middle school located in the 90 municipalities participating in PrevHPV research (secondary objective 2),
- (iii) GPs practicing in the municipalities randomized to groups 1, 2, 5 and 6 (secondary objective 2).

- **Others affected by this research**

Furthermore, National Education professionals as well as stakeholders (for example health students) who will participate in the various actions will be questioned using satisfaction questionnaires.

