#### **7.4. Evaluation of the effect on knowledge, attitudes, beliefs and practices**

The repeated cross-sectional survey (before - after) KABP-6C is carried out in the following populations:

- Adolescents (girls and boys), enrolled in Grades 8 & 9 classes in middle schools (public and private) located in the 90 participating municipalities.
- Parents of adolescents (girls and boys), enrolled in middle schools (public and private) located in the 90 participating municipalities.
- GPs practicing in municipalities in groups 1, 2, 5 and 6.

(i) KABP-6C survey among middle school students and their parents:

With authorization from the principals/directors of each middle school, the information and the invitation to the survey will be communicated to families through the middle school's usual means of communication. Parents may object to their child's participation. The T0 (before) and T1 (after intervention) questionnaires, self-administered and online, will be accessible via a specific research internet link.

The adolescent questionnaires will be administered in class under the supervision of a teacher or health professional. Each participant will be assigned an inclusion number, determined in advance by the middle school referent, to be entered in the T0 and T1 questionnaires which will make it possible to establish the link between the pre- and post-intervention questionnaires (T0 and T1). During the T0 survey, students will be asked to note this number in their correspondence notebook. A list of inclusion numbers and student names will be established for each class. All lists of the different classes will be kept in a closed envelope in the locked office of the research referent in the establishment, until they are transferred to the classes at T1. On this occasion, school staff present in class for the T1 questionnaire will be able to remind students of their inclusion number.

Parents will receive a survey invitation with the link to the research site. They will complete the T0 and T1 questionnaires at home, without the presence of children. Parents will be asked to enter their child's inclusion number (given in class and noted in the correspondence book), in order to be able to establish the family link while remaining anonymous. Parents will also be asked to note this inclusion number and keep it until the T1 survey.

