The correspondence between inclusion number (which will make it possible to establish the link between T0 and T1, and between children and parents) and the identity of the participants will only be documented in the students' individual correspondence notebook and on the list kept for each class by the middle school's research referent. These lists will be destroyed after the questionnaires are administered to T1 in each class. Investigators will not have access to these lists.

(ii) KABP-6C survey among GPs:

For each of the municipalities in groups 1, 2, 5, and 6 the list of GPs practicing within each of them is established. These GPs are then contacted by telephone to ask them to participate in the KABP-6C survey. Each participant will be assigned an inclusion number which will make it possible to establish the link between the pre- and post-intervention questionnaires (T0 and T1).

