### **11.3.2. Analysis of secondary outcomes**

#### **(i) Analysis of secondary objective 1**

For the analysis of this objective, people with a positive change in intention/vaccination will be identified (change from “no” for both at T0 to “yes” for one of the two at T1).

The variables corresponding to the KABP-6C items will be created in particular by calculating knowledge scores and Likert scale medians.

For an analysis of T0, the percentages and medians of the items will be presented by intervention group, namely:

- a. By EMM groups 0 and 1, among participants without vaccination campaign, without taking into account the GP intervention
- b. By school interventions (campaign + EMM vs. without campaign or EMM), without taking into account the GP intervention
- c. By GP groups 0 and 1, among participants with EMM, without taking into account the vaccination campaign intervention

For an analysis of the main effects, the percentages of people with change and the medians of the differences will be presented by group (see a., b., and c.).

The differences will be tested first by suitable non-parametric tests (Fisher's and Wilcoxon, ranksum).

Multilevel models with a binary or continuous (linear) dependent variable will then be constructed in order to estimate the effect of interventions alone or in interaction, while taking into account intraclass correlation effects (cluster randomization). The interactions to be studied as a priority are:

- between the GP intervention and the school intervention (EMM+campaign),

- between the vaccination campaign intervention and the GP intervention (only possible in combination with EMM)
- between the EMM intervention and the GP intervention (only possible in the absence of a vaccination campaign)

For an analysis not taking into account individual evolution between T0 and T1, the effect of each intervention (alone or in interaction) will be estimated from a difference-in-difference model, i.e. including an interaction between the intervention group (among the 6 defined, with the control group as reference) and the temporal indicator “after” (vs. before) intervention.

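### For GP outcomes, the three contrasts and three priority interactions planned for secondary objective 1 are empty, mixed or inestimable, because GPs are surveyed only in groups 1, 2, 5 and 6

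*Protocol*

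**What the plan says.** Protocol 2.2 sets secondary objective 1 as the effect of the components, alone or combined, on "the vaccination intention of adolescents, parents and GPs" and on their knowledge, attitudes, beliefs and practices.

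Students and parents are surveyed in all 90 municipalities. GPs are not. Section 4.2 limits the GP questionnaire to "GPs practicing regular consultations with adolescents in the 60 municipalities of groups 1, 2, 5 and 6". Section 7.4 repeats this ("GPs practicing in municipalities in groups 1, 2, 5 and 6") and draws up the contact list the same way ("For each of the municipalities in groups 1, 2, 5, and 6 the list of GPs practicing within each of them is established"). Section 5.1 evaluates the effect on "GPs practicing in the municipalities randomized to groups 1, 2, 5 and 6". The restriction is stated consistently and is not a slip.

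Section 11.3.2 (i) then gives a single analysis for the whole objective:

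- contrast a: EMM yes or no, where there is no vaccination campaign, ignoring GP training;
- contrast b: campaign plus EMM against neither, ignoring GP training;
- contrast c: "By GP groups 0 and 1, among participants with EMM, without taking into account the vaccination campaign intervention";
- first-stage non-parametric tests on these contrasts, followed by multilevel models;
- three priority interactions, each involving GP training, the first being the one "between the GP intervention and the school intervention (EMM+campaign");
- a difference-in-difference model with the six-level group factor and control as reference.

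No separate analysis is given for GPs.

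**The concern.** The contrasts and interactions were worked out for a six-group data set. The section even notes where each of the last two interactions can be studied. The GP survey has only four groups. Groups 3 and 4 ("Group 3 - EMM + Facilitation of access" and EMM alone) are the only ones that combine EMM with untrained GPs, and their GPs are never asked.

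If the section is followed as written for GPs, one contrast cannot be computed. Two others are labelled as school-component effects but include part of the training effect. The interactions named as priorities drop out of the model. Training is the one component aimed at GPs, so a reader of the GP results could credit EMM or the campaign with what the training did.

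**Working it through.** **Inputs.** Six groups of 15 municipalities (4.2). Components per group (4.2, 5.1), coded E = EMM, G = GP training, F = facilitated access (the campaign):

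| Group | E | G | F | GPs surveyed |
|---|---|---|---|---|
| 1 | 1 | 1 | 1 | yes |
| 2 | 1 | 1 | 0 | yes |
| 3 | 1 | 0 | 1 | no |
| 4 | 1 | 0 | 0 | no |
| 5 | 0 | 1 | 0 | yes |
| 6 | 0 | 0 | 0 | yes |

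**The plan's own figure.** 4 surveyed groups × 15 = 60 municipalities, as 4.2 states.

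**Contrasts.** Write the group mean as m + E·e + G·t + F·f (additive effects e, t, f; groups of equal size).

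Students and parents, all six groups:
- a: (2+4) vs (5+6) = e. Training is 50% on both sides.
- b: (1+3) vs (5+6) = e + f. Training is 50% on both sides.
- c: (1+2) vs (3+4) = t.

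GPs, groups 1, 2, 5 and 6:
- a: 2 vs (5+6) = (m + e + t) − (m + t/2) = e + t/2. Training is 100% vs 50%.
- b: 1 vs (5+6) = (m + e + t + f) − (m + t/2) = e + f + t/2. Training is 100% vs 50%.
- c: (1+2) vs no group. Not computable.

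The Protocol gives no training effect on GPs. As an assumption, if e = 0 and t is 5, 10 or 20 percentage points, contrast a shows 2.5, 5 or 10 points under the EMM label.

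**Interactions, by the groups each one needs.**
- GP training × (EMM + campaign): groups 1, 3, 5, 6. Group 3 is missing.
- Campaign × GP training, within EMM: groups 1, 2, 3, 4. Groups 3 and 4 are missing.
- EMM × GP training, no campaign: groups 2, 4, 5, 6. Group 4 is missing.

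In algebra, over groups 1, 2, 5, 6: E×G = (1, 1, 0, 0), which is the same column as E; and F×G = (1, 0, 0, 0), which is the same column as F.

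**Design-matrix rank (with intercept).**

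| Terms | All six groups | GP groups 1, 2, 5, 6 |
|---|---|---|
| E, G, F | 4 of 4 | 4 of 4 |
| + E×G | 5 of 5 | 4 of 5 |
| + F×G | 5 of 5 | 4 of 5 |
| + both | 6 of 6 | 4 of 6 |

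Neither interaction is estimable for GPs. With both in the model, only the intercept and the training effect (5 vs 6) can still be identified.

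**What remains for GPs.** Four group means give three independent comparisons: 5 vs 6 (training without EMM), 2 vs 5 (EMM given training) and 1 vs 2 (access given EMM and training). Combinations of these follow, including 2 vs 6 and 1 vs 6.

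**Precision of the remaining training comparison.** Counting municipalities only, the variance for 15 vs 15 is proportional to 1/15 + 1/15 = 0.133. For contrast c as students and parents have it, 30 vs 30, it is 1/30 + 1/30 = 0.067. The ratio of standard errors is √2 = 1.41.

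**The case against.** The strongest reply is that contrasts a to c were never meant for GPs. The section opens with change in intention or vaccination, and GPs have no outcome of being vaccinated. EMM participants are students and parents. On that reading the GP analysis is simply left to a later plan. This is plausible for the change variable. But the section is headed as the analysis of an objective that names GPs, it gives no other analysis for them, and it does not say that the contrasts are limited to the other two populations.

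Three stronger inferences are tempting, and the reply is right against each.

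- *That the plan cannot assess components alone or combined for GPs.* It can in part. The difference-in-difference model, run with four group levels, gives 5 vs 6, 2 vs 6 and 1 vs 6.
- *That the whole plan would credit training effects to EMM.* The mixing affects the descriptive results and first-stage tests by contrasts a and b. A main-effects multilevel model has full rank and separates the components, though only by assuming no interaction, which these data cannot test.
- *That the loss of precision is √3 = 1.73.* That ratio uses a 45 vs 45 benchmark. Contrast c is restricted to EMM, so its benchmark is 30 vs 30.

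It is also fair that this concerns one respondent population in one secondary objective, and that 11.3.2 (i) applies no predefined significance level.

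**Conclusion.** The section is wrong as written for GP outcomes, and only for those. Contrast c has no untrained GPs. Contrasts a and b add about half of the training effect to the school-component effect. None of the three priority interactions is estimable. The empty contrast and the lost interactions follow from the Protocol's group definitions alone. The factor of one half also needs additive effects and equal group sizes, and it refers to allocation of municipalities, not to how many GPs take up the training. The point amounts in these illustrations to 2.5 to 10 points for an assumed training effect of 5 to 20 points.

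Training alone and the two combined packages can still be compared with control. The primary outcome and the student and parent analyses are not affected. A reader might conclude that the four-group GP survey is itself an error; the documents do not support that, since the restriction is deliberate and repeated. What fails is its match with the analysis text.

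**What to change.** In 11.3.2 (i), state that contrasts a to c and the three priority interactions apply to students and parents only. Add a short paragraph for GP outcomes, using multilevel models adjusted for the T0 response, that prespecifies:

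- 5 vs 6: training without EMM;
- 2 vs 5: EMM given training;
- 1 vs 2: facilitated access given EMM and training;
- 2 vs 6 and 1 vs 6: the combined packages against control.

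Keep 2 vs 5 and 1 vs 2 separate. Pooling groups 1 and 2 against 5 would mix EMM with facilitated access. State that the group factor has four levels for GPs and that interactions with training cannot be estimated for their outcomes.

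The cost is wording, with no new data. The small downside is that the training effect within EMM, and any synergy with training, are no longer claimed for GPs. Extending the GP survey to groups 3 and 4 is not part of this change.

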## 4. STUDY DESIGN

### 4.1. Type of research

The PrevHPV trial is a multicenter cluster randomized controlled trial with a 6-arm partial factorial design. The geographical areas covered by the trial correspond to the academies of Aix-Marseille, Clermont-Ferrand, Créteil, Grenoble, Lille, Limoges, Lyon, Nancy-Metz, Nantes, Reims, Strasbourg, Toulouse, Orléans-Tours, and Versailles. These academies were selected to have a diversity of profiles (geographic, behavior/vaccination) across mainland France, in collaboration with the General Directorate of School Education. Within the geographical areas covered by the trial, eligible municipalities are then identified (based on their characteristics and the participation of middle schools in the trial). The cluster, which is the randomization and evaluation unit, correspond to all the inhabitants in a municipality (identified by an administrative code, «code commune»).

The use of a factorial design makes it possible to evaluate the effect of each component of the intervention in isolation (compared to the absence of intervention and between each other), but also the effect of the association of the different components to identify whether it is additive, synergistic or antagonistic.

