### **11.3.1. Analysis of the primary outcome**

The prevalence of vaccination (at least 1 dose received and complete vaccination) among adolescents aged 11-14 is calculated (from SNDS data, supplemented where appropriate with data from vaccination centers, family planning centers and vaccines delivered in middle school) at the different measurement times (before intervention, 2 months, 6 months and 12 months after intervention) and in each of the six study groups. A calculation of this prevalence according to the sex and deprivation level of the municipality of residence of the adolescents is also planned.

Concerning the analysis of the primary outcome (vaccination coverage rate), an analysis at the cluster level will be carried out, that is to say that the unit of analysis will be the municipality and not the adolescent who is nested in his or her municipality. The data will be collected at the municipality level. Each municipality (= cluster) will be weighted by its size. A modeling approach will be used, carrying out a global analysis of the 90 randomization units. The model will be a linear model in which we will consider 3 fixed effects (one per component) and potential interactions between component. The baseline VC will be considered as an adjustment variable.

The evolution of the VC over time (M2, M6, M12) will also be modeled by considering a longitudinal model, and adjusting for the baseline VC rate.

Subgroup analyzes will be carried out according to sex, deprivation level (FDep) and considering a modeling approach with interaction terms.

Depending on the quality of the data reported by vaccination centers and family planning centers, sensitivity analyzes will be carried out to take into account only SNDS data and the number of vaccines delivered in middle school.

The analyzes are carried out using SAS software version 9.4 or later (SAS Institute Inc.) or R, and considering two-sided statistical tests and a level of significance of 5%.

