Variations in the impact of intervention components will be explored by analyzes stratified by individual characteristics and KAP-6C (at T0). In order to test for significant differences between subgroups, we will examine 95% confidence intervals. In general, we will neither apply predefined statistical significance levels nor correct for multiple testing, but report exact P values. Interaction terms may be included in the models, if indicated.

Models including individual characteristics will be built for an analysis of the determinants of vaccination intentions.

Other analyzes will focus on the change from “intention without vaccination” to “vaccination declaration”; and on the association between individual characteristics, KAP-6C items at T0 or T0-T1 change.

Statistical analyzes will be carried out using STATA software.

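### Secondary objective 1 first tests KABP-6C changes on individual respondents, ignoring randomisation by municipality, and does not say that the later multilevel models supersede those P values

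*Protocol*

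**What the plan says.** Section 4.1 of the protocol fixes the unit: "The cluster, which is the randomization and evaluation unit, correspond to all the inhabitants in a municipality". Section 4.2 describes the instrument for secondary objective 1 as "A KABP-6C survey, at the individual level, repeated cross-sectionally (pre and post interventions"), so the data are individual responses nested in municipalities.

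Section 11.3.2(i) defines three pooled comparisons, a to c. For each it presents the percentage of people with a positive change and the median difference. These differences are to be "tested first by suitable non-parametric tests", named as Fisher's test and the Wilcoxon rank-sum test. The next sentence introduces multilevel models that estimate the intervention effects "while taking into account intraclass correlation effects (cluster randomization").

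On reporting, the same section says "we will neither apply predefined statistical significance levels nor correct for multiple testing, but report exact P values". On effect modification it plans stratified analyses and adds: "In order to test for significant differences between subgroups, we will examine 95% confidence intervals". Interaction terms are mentioned only as something that may be added where indicated.

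**The concern.** Fisher's exact test and the rank-sum test both assume independent observations. Respondents in one municipality share schools, teachers, doctors and the allocated intervention, so their answers are likely to be correlated. The tests then understate the variance of the group difference, and the P value is too small.

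The plan will report exact P values without multiplicity correction, so a reader has no other protection against a miscalibrated one. Each contrast could also carry two P values, one from a test that ignores the design and one from a model that respects it. The text does not call the former descriptive, and it does not say which one counts if they disagree.

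The subgroup sentence has a related weakness. It speaks of testing for significant differences but names no test of the difference, and the proper one, an interaction term, is left optional.

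**Working it through.** **1. The plan's own figure.** Section 11.2 gives the only intra-class correlation in the document, and it is for vaccination coverage. Inputs: ICC 0.05, mean cluster size 466, coefficient of variation 0.5, prevalence 0.161 × 0.4885 = 7.86%, a 10-point increase, two-sided 5%, 90% power.
- Individually randomised size: 234 per arm.
- Design effect: 1 + ((1 + 0.5²) × 466 − 1) × 0.05 = 30.08.
- Clusters per group: 234 × 30.08 / 466 = 15.1. Power with 15 clusters is 89.9%.

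The stated 15 per group reproduces. The value 0.05 thus belongs to the coverage outcome; nothing comparable is given for KABP-6C.

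**2. The contrasts.** For students and parents, who are surveyed in all six groups of 15 municipalities, each pooled comparison is 30 against 30:
- a: groups 2 and 4 against 5 and 6
- b: groups 1 and 3 against 5 and 6
- c: groups 1 and 2 against 3 and 4

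GPs are surveyed in groups 1, 2, 5 and 6 only. The formula in step 4 does not depend on the number of clusters.

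**3. Assumptions.** Respondents per municipality, m, are not stated. I take 20 to 100 for students and parents and 2 to 10 for GPs. An upper extreme for students is 233, half of 466, if all Grade 8 and 9 pupils of a single school answered. I take ICC 0.01 and 0.05, the latter borrowed from section 11.2. Cluster sizes are taken as equal.

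**4. Error rate of a test that ignores clustering.** With DE = 1 + (m − 1) × ICC, the true two-sided rate at nominal 5% is 2 × [1 − Φ(1.96 / √DE)]. Example: m = 20, ICC 0.05 gives DE = 1 + 19 × 0.05 = 1.95 and a rate of 16.0%.

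| m | DE, ICC 0.01 | Rate | DE, ICC 0.05 | Rate |
|---|---|---|---|---|
| 2 | 1.01 | 5.1% | 1.05 | 5.6% |
| 10 | 1.09 | 6.0% | 1.45 | 10.4% |
| 20 | 1.19 | 7.2% | 1.95 | 16.0% |
| 50 | 1.49 | 10.8% | 3.45 | 29.1% |
| 100 | 1.99 | 16.5% | 5.95 | 42.2% |
| 233 | 3.32 | 28.2% | 12.60 | 58.1% |

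**5. Simulation check.** I simulated 30 against 30 municipalities with no true effect: 1,500 runs for Fisher (15% with change) and 600 for rank-sum.
- ICC 0.05, Fisher / rank-sum: 8.3% / 10.8% (m = 10), 13.5% / 15.2% (20), 27.2% / 30.3% (50), 41.2% / 39.2% (100).
- ICC 0.01: 4.0% / 5.2%, 6.5% / 6.8%, 10.1% / 10.8%, 15.5% / 15.5%.

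These agree with the formula, with Fisher somewhat conservative at small m.

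**6. Unequal sizes.** Using the coefficient of variation of 0.5 from section 11.2 at ICC 0.05, the rates rise to 18.6%, 33.2% and 46.5% for m = 20, 50 and 100.

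**7. Effect on one reported P value.** An unadjusted P of 0.01 (z = 2.576) becomes about 0.065 after dividing z by √1.95 (m = 20, ICC 0.05), about 0.17 with √3.45 (m = 50, ICC 0.05), and about 0.035 with √1.49 (m = 50, ICC 0.01).

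**The case against.** The strongest reply is that the authors saw the problem. The sentence after the tests assigns effect estimation to multilevel models that allow for cluster randomisation, so the preliminary tests can be read as a first look. That largely stands. A reader might infer that this objective is analysed without regard to clustering; the protocol does not support that. What remains is that the text neither labels the tests descriptive nor gives the models precedence.

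A second reply is that no significance threshold applies here. The 5% level in section 11.3.1, "considering two-sided statistical tests and a level of significance of 5"%, is stated under the primary outcome, so 5% in the working is a yardstick and not this objective's decision rule. That is right, but exact P values are promised, and exact P values from these tests are miscalibrated whatever the threshold.

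Third, no single error rate can be read from the protocol. The tests concern changes from T0 to T1, and differencing can remove stable differences between municipalities, so the correlation could be well below 0.05. That stands, and is why a range is given. In the other direction, section 7.4 has pupils complete the questionnaire in class, which makes many respondents per municipality likely.

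Two further inferences should be resisted. One is that dozens of items would be falsely significant: the questionnaire is in an appendix that is not shown, so the number of items tested is unknown. The other is that subgroup effects are judged by whether two intervals overlap. Such a rule would have a true level of about 0.6% for equal, independent intervals, but the protocol states no overlap rule, calls the work exploratory and already permits interaction terms.

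**Conclusion.** The point holds in limited form. Applied to individual respondents, the Fisher and rank-sum tests give P values that are too small wherever the ICC is positive and several respondents share a municipality. The direction is certain under those conditions; the size rests on the assumed respondent numbers and ICCs. It is material for students and parents across most of the assumed range, and small for GPs unless the ICC and the number per municipality are both at the top of theirs. Nothing here touches the primary analysis, which section 11.3.1 carries out at municipality level. Because this is a preliminary test on a secondary objective, followed by a suitable model, the severity is minor to moderate. The subgroup sentence is loosely worded rather than shown to be wrong, and should be tightened at the same time.

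**What to change.** In section 11.3.2(i):
- Delete the individual-level Fisher and rank-sum tests, or present those comparisons descriptively without P values.
- State that all P values for this objective come from the multilevel models with a municipality random effect.
- If a non-parametric check is wanted, run it on municipality-level percentages or medians.
- Make the treatment-by-subgroup interaction term in the multilevel model the test of subgroup differences. Stratum-specific 95% confidence intervals can still be shown as description.

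The cost is a change of wording; no new data are needed. The downside is that some P values will be less favourable.
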